### 8.4.2 Overall survival (OS)

OS is defined as the time from the date of randomization to death from any cause. For the patients who are alive at the end of the study, the date of the last contact is used for analysis.

### 8.4.3 Pathologic outcomes

Pathologic outcomes are defined as TME quality, negative CRM and negative DRM, length of proximal resection margin (PRM), length of DRM, and the number of retrieved lymph nodes.

#### **8.4.4 30-day postoperative complications**

Thirty-day postoperative complications included any complications occurring within 30 days after surgery. Postoperative complications were graded according to the Clavien-Dindo classification. Severe complications were defined as Clavien-Dindo III-V.

#### **8.4.5 30-day postoperative mortality**

Thirty-day operative mortality is defined as deaths occurring from any cause during the first 30 postoperative days.

#### **8.4.6 Operative outcomes**

- **Conversion to Open Surgery**

The conversion is defined as any part of the mesorectal dissection using the traditional open surgery. The surgeon decided on the conversion after considering patient safety, technical difficulties, and relevant conditions influencing the completion of TME.

- **Operative time**

Operative time is defined as the time from skin incision to the completion of skin suture.

- **Estimated blood loss**

Estimated blood loss will be measured according to the suction and the weight of wet gauze, and then minus the irrigation.

- **Intraoperative outcomes**

Intraoperative outcomes are defined as events occurring during surgery and details of the surgical procedure, such as conversion, operative time, estimated blood loss, type of surgery, and diverting ostomy creation.

#### **8.4.7 Postoperative outcomes**

- **Time to first flatus**

Time to first flatus is defined as the time from surgery completion to the first occurrence of flatus during the subject's postoperative recovery (measured in hours).

- **Time to the first defecation**

Time to the first defecation is defined as the time from skin closure to the time of time to first defecation (measured in hours)

- **Time to the liquid diet**

Time to a liquid diet is defined as the time from surgery completion to the resumption clear liquid diet (measured in hours)

- **Time to the normal diet**

Time to normal diet is defined as the time from surgery completion to the resumption of the normal diet (measured in hours)

- **Length of hospital stay**

Duration of hospital stay is measured from the day of surgery until the day of discharge from the hospital

## **9. The flow of study**

An academic advisory committee supervised by the principal investigator of the study will be established.

Before starting the study, surgeons participating in the study will receive training on standard operating procedures and a surgical training certificate provided by the academic advisory committee. All hospitals participating in this study shall provide copies of qualification certificates/licenses and personal legal certificates. All materials shall be bound together for document management. All doctors participating in this study shall provide copies of the qualification certificates, which will be documented.

### **9.1 Randomization**

This study uses a dynamic randomization technique based on variance minimization. Patients are stratified by clinical tumor stage (stage I, II, or III), age ( $\leq 44$  years, 45-59 years, or  $\geq 60$  years), sex, body mass index (BMI) ( $\leq 23.9$  kg/ m^2, 24-27.9 kg/ m^2, or  $\geq 28$  kg/ m^2), and ASA classification (I, II, or III). Random numbers are generated and assigned to patients by a computerized central randomization system called the Distributed Annotation System (DAS) for interactive web response system (IWRS) for treatment randomization following the principle of central competition. After the last participant has been assigned a random number, the researcher responsible for randomization derives the randomization table from the randomization system and submits it to the sponsoring organization. Two sealed copies of each randomization table are stored in the national institution on clinical trials of drugs to which the principal investigator belongs and the sponsoring organization.

After each participant is approved as eligible, a researcher logs in to the DAS for IWRS, enters the participant's information, including initials, sex, and age, applies for randomization into the treatment group, and then fills the random number into the medical record of the study.

### **9.2 Screening of participants**

All participants must have a definitive histopathological diagnosis. Their tumors must have been clinically staged through pelvic MRI or, if possible, the combined use of pelvic MRI and endorectal ultrasound. Patients who meet the inclusion criteria and cannot be excluded are considered potential participants based on the exclusion criteria.

**Stage I patients:** The doctors in charge inform the participants and their families about the study, explain the differences between the two surgical approaches, and ask whether they agree to be randomized into one of the two groups. Patients who agreed to be randomized signed informed consent and were enrolled in the study.

**Stage II or III patients:** After filling out **The Participant Screening Form,"** patients are treated with preoperative chemoradiotherapy and given preoperative examinations 6-7 weeks after the completion of radiotherapy. Patients who fully meet the inclusion criteria and cannot be excluded are considered potential participants based on the exclusion criteria. The doctors in charge informed the participants and their families about the study explained the differences between the two surgical approaches, and asked whether they agreed to be randomized into one of the two groups patients who agreed to be randomized signed informed consent and were enrolled in the study.

### **9.3 Inclusion of participants**

Only the patients who fully meet the inclusion criteria will be included in the study; those who meet any exclusion criteria will not be included.

### **9.4 Management of patient participation**

Five days before randomization, patients who meet the inclusion criteria complete the following examinations and questionnaires:

- 1) Complete blood count, urinalysis, stool analysis, fecal occult blood tests
- 2) Biochemical examination (including liver and kidney function, electrolytes, blood glucose, and blood lipid levels), blood type, coagulation function, digestive tract tumor markers (CEA and CA199), screening for infectious diseases (hepatitis B, hepatitis C, AIDS, syphilis, etc.)
- 3) X-ray examination or non-contrast-enhanced chest CT scan; contrast-enhanced scan if needed
- 4) Electrocardiogram (ECG)
- 5) Enhanced liver/pelvic MRI scan, which can be combined with endorectal ultrasound or endoscopic ultrasound if possible
- 6) Echocardiography, pulmonary function, and other examinations according to the patient's condition if necessary
- 7) Serum or urine pregnancy tests in women of childbearing age
- 8) Bladder function assessment: the residual urine volume in the bladder and the I-PSS
- 9) Quality of life (QoL) assessment: EORTC QLQ C30 and EORTC QLQ CR29
- 10) Sexual function assessment: the IIEF-5 and the FSFI
- 11) Assessment of anorectal function (for those who plan to preserve or partially preserve the anal sphincter): Anorectal pressure, rectal sensory function, anorectal reflexes, and fecal incontinence (Wexner score)

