## **3. Participants**

Eligible participants are the patients who have an initial diagnosis of rectal cancer within 5 cm from the dentate line (by rigid proctoscopy). Clinical staging is determined by computed tomography (CT), endorectal ultrasound, and pelvic magnetic resonance imaging (MRI). No distant metastasis can be detected. No contraindication to general anesthesia. The participating patients have cT3/T4aN0M0 or cT1-4aN1-2M0 low rectal cancer without contraindications to preoperative radiotherapy or chemotherapy. Low rectal cancer is defined as a rectal adenocarcinoma with a lower margin within 5 cm from the dentate line as determined by rigid proctoscopy at diagnosis.

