### **6.1.2 Preoperative radiotherapy protocol**

(1) Definition of target areas: The primary tumor and regional lymphatic drainage area's high-risk recurrence area must be irradiated. The high-risk recurrence areas of primary tumors include the tumor/tumor bed, the mesorectal region, and the presacral region. The target area for radiation treatment of carcinoma of the low rectum should include the ischiorectal fossa.

The regional lymphatic drainage areas include the lymphatic drainage area of the common iliac vessels in the true pelvis, the mesorectal region, the lymphatic drainage area of the internal iliac vessels, and the obturator lymph node area.

Radiation therapy techniques: According to the radiotherapy equipment available in the hospital, different techniques can be chosen, including conventional radiotherapy, three-dimensional (3D) conformal radiotherapy, intensity-modulated radiotherapy (IMRT), and image-guided radiotherapy.

CT simulation is recommended for radiotherapy treatment planning. If CT simulation is unavailable, conventional simulation must be performed. Patients should be placed in the prone or supine position with a full bladder.

Patients must receive irradiation in three or more fields.

If IMRT is necessary, the radiation treatment plan must be validated.

Local dose enhancement can be achieved through intraoperative or external irradiation.

Irradiation dose: The irradiation dose and schedule must be clearly defined regardless of which radiation therapy technology (conventional radiotherapy or new techniques, such as 3D conformal radiotherapy and IMRT) is used. The volumetric dose is defined for 3D conformal radiotherapy planning and IMRT, while the isocenter dose should be defined for conventional radiotherapy planning.

The protocol recommended for the high-risk recurrence area of the primary tumor and the regional lymphatic drainage area is a total dose (DT) of 45.0-50.4 Gy in 1.8-2.0 Gy per fraction for 25 or 28 fractions.

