### **6.1.3 Preoperative chemotherapy during the interval between preoperative chemoradiotherapy and surgery**

As recommended by the academic advisory committee, an addition of preoperative capecitabine chemotherapy (1250 mg/ m^2, twice a day for 14 days) was performed between the end of radiotherapy and surgery.

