## Appendix 2: Assessment schedule and process

### Assessment schedule for the screening/treatment period

|                                             | Screening:
14 days through
1 day before
neoadjuvant
radiotherapy | Screening: 5 days
before
randomization | Adjuvant therapy                             |                                 |
|---------------------------------------------|------------------------------------------------------------------------------|----------------------------------------------|----------------------------------------------|---------------------------------|
|                                             |                                                                              |                                              | Adjuvant chemotherapy                        | Adjuvant
radiotherapy        |
| Treatment plan                       |                                                                              |                                              | 7-1 days before each
chemotherapy session | 7-1 days before
radiotherapy |
| Informed consent                            |                                                                              | ×                                            |                                              |                                 |
| Demographic data                            | ×                                                                            | ×                                            |                                              |                                 |
| Medical history (a)                         | ×                                                                            | ×                                            |                                              |                                 |
| General physical
examination             | ×                                                                            | ×                                            | ×                                            | ×                               |
| Height, weight, body
surface area (BSA)  | ×                                                                            | ×                                            | ×                                            | ×                               |

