| ECOG PS score                               | ×                                                                            | ×                                            | ×                                            | ×                               |
| Concomitant diseases
& Treatment         | ×                                                                            | ×                                            |                                              |                                 |
| Complete blood
count                     | ×                                                                            | ×                                            | ×                                            | ×                               |
| Blood biochemistry                          | ×                                                                            | ×                                            | ×                                            | ×                               |
| Coagulation test                            |                                                                              | ×                                            |                                              |                                 |
| Pregnancy test (if
applicable)           |                                                                              | ×                                            |                                              |                                 |
| Tumor markers (b)                           | ×                                                                            | ×                                            |                                              |                                 |
| ECG                                         | ×                                                                            | ×                                            | ×                                            | ×                               |
| Echocardiography (c)                        |                                                                              | ×                                            |                                              |                                 |

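### Stage II/III women have no scheduled pregnancy test until after pelvic chemoradiotherapy

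*Combined protocol and SAP*

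**What the plan says.** Protocol section 9.4 opens with "Five days before randomization, patients who meet the inclusion criteria complete the following examinations and questionnaires"; item 7 of the list that follows is "Serum or urine pregnancy tests in women of childbearing age".

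The first table of Appendix 2 has two screening columns. One is headed "14 days through 1 day before neoadjuvant radiotherapy"; the other is five days before randomization. The row beginning "Pregnancy test (if applicable" is blank in the first and ticked in the second. It is also blank in both adjuvant-therapy columns, and the follow-up table has no such row.

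For stage II/III, section 9.2 says that after the screening form is filled out "patients are treated with preoperative chemoradiotherapy and given preoperative examinations 6-7 weeks after the completion of radiotherapy". Consent and enrolment follow.

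The treatment given before that visit is set out in section 6.1:

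- Radiotherapy (6.1.2): "45.0-50.4 Gy in 1.8-2.0 Gy per fraction for 25 or 28 fractions".
- Concurrent 5-FU-based chemotherapy (6.1.1), with five weeks of capecitabine recommended.
- A further capecitabine course (6.1.3), "twice a day for 14 days) was performed between the end of radiotherapy and surgery".

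Two eligibility statements bear on the point. Section 3 describes the stage II/III participants as having "low rectal cancer without contraindications to preoperative radiotherapy or chemotherapy". Exclusion criterion 7 (section 3.2) removes women of childbearing age who test positive at baseline or have not been tested. It does not define baseline.

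**The concern.** A pregnancy test protects against an exposure only if it is done first. Here the main fetal hazards for stage II/III women are pelvic irradiation and a fluoropyrimidine, and the only test on the schedule comes after both. A site that follows Appendix 2 to the letter can start radiotherapy in an untested woman and find a pregnancy only once the exposure has happened. The late test still does something useful: it satisfies exclusion criterion 7 at enrolment and keeps pregnant women out of randomization and trial surgery. It cannot support the section 3 requirement, which has to be met before chemoradiotherapy starts.

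The stake is participant safety. Nothing in the sample size, the randomization or the primary analysis depends on it.

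**Working it through.** The plan gives no figure of its own to reproduce. The check sets the schedule beside the treatment sequence, then does some simple arithmetic.

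**Sequence for stage II/III** (sections 9.2, 6.1 and 6.2; Appendix 2)

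| Step | Timing | Pregnancy test scheduled? |
|---|---|---|
| Pre-radiotherapy screening | 14 to 1 days before radiotherapy | No |
| Radiotherapy with concurrent chemotherapy | 25 or 28 fractions | No |
| Interval capecitabine, 14 days | Between radiotherapy and surgery; start not dated | No |
| Pre-randomization examinations | 6-7 weeks after radiotherapy ends | Yes, the only one |
| Randomization, then surgery | Surgery 6-8 weeks after radiotherapy ends | No |

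**Delay from first exposure to test.** The documents do not state fractions per week; five is assumed.

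- Length of radiotherapy: 25 / 5 = 5.0 weeks, or 28 / 5 = 5.6 weeks.
- First fraction to test: 5.0 + 6 = 11.0 weeks, up to 5.6 + 7 = 12.6 weeks.
- Pre-radiotherapy visit to test: 11.0 + 1/7 = 11.1 weeks, up to 12.6 + 14/7 = 14.6 weeks.

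The conclusion that the test comes after chemoradiotherapy does not depend on the assumed fractionation. Section 9.2 alone puts it at least six weeks after radiotherapy ends.

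**Interval capecitabine.** The course lasts two weeks. It is finished before the test if it starts by week 6 - 2 = 4 after radiotherapy (test at week 6) or week 7 - 2 = 5 (test at week 7). Because the start is not dated, it has probably, but not certainly, been given by then.

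**What the earlier visit already covers.** Counting the Appendix 2 rows ticked in either screening column:

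- Both visits: 14 rows, including blood count, biochemistry, ECG and pelvic MRI.
- Pre-randomization visit only: 11 rows. These are informed consent (1); coagulation, echocardiography and pulmonary function (3); two quality-of-life scores, residual urine, I-PSS, IIEF-5 and FSFI (6); and the pregnancy test (1).
- Total: 14 + 11 = 25.

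Of those 11 rows, ten concern consent, fitness for surgery or functional baselines, which belong naturally before surgery. The pregnancy test is the one that bears directly on whether pelvic irradiation may start.

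**Stratum concerned.** Section 5 requires 609 stage II/III patients out of 968, and 609 / 968 = 62.9%. This is the size of the stratum, not of the affected group. It includes men and women past childbearing age, and a woman found pregnant would not be among those randomized.

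**The case against.** The strongest reply is that eligibility is already checked before chemoradiotherapy. Section 9.2 applies the inclusion and exclusion criteria in its opening paragraph, before it divides by stage, and repeats the check for stage II/III after radiotherapy. An untested woman would fail exclusion criterion 7 at the first check, and section 3 separately bars contraindications. On that reading Appendix 2 merely omits how an existing criterion is verified.

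The reading is possible, but it depends on an undefined baseline and on a screening form that is not reproduced. It also sits badly with section 9.4 and Appendix 2, the two places that time the test. Both put it before randomization only, so a stray missing tick is unlikely. Section 3 names no test.

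A second reply is that chemoradiotherapy precedes trial consent and that centers may test under routine care. They may; the documents do not say. The finding is that the protocol schedules no test, not that none would be done. The protocol also places chemoradiotherapy under its own intervention section and specifies 14 assessments at the pre-radiotherapy visit, so the work-up there is within its scope.

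Three limits stand. The affected group may be very small. The 62.9% says nothing about its size. And the gap is wider than the pre-radiotherapy visit: section 9.8.2 recommends adjuvant chemoradiotherapy for pT3-4 or N1-2 patients who had no preoperative radiotherapy, which can include women staged clinically as I, and no test is scheduled near that treatment either. This last point extends the remedy; it does not weaken the finding.

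**Conclusion.** The concern holds. For stage II/III women of childbearing age, the only scheduled pregnancy test follows pelvic radiotherapy and concurrent fluoropyrimidine, by about 11.0 to 12.6 weeks from the first fraction at an assumed five fractions per week. The finding rests on two agreeing statements of when the test is done and on the order of events in section 9.2. The number of women affected is unknown, because the documents give no sex or age distribution. The comparison of surgical approaches is untouched. It is worth correcting because the potential harm cannot be reversed and prevention costs very little.

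**What to change.** Three edits to the protocol:

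1. **Appendix 2, first table:** tick the pregnancy test, for women of childbearing age, in the pre-radiotherapy screening column.
2. **Section 9.2, stage II/III paragraph:** state that a serum or urine test is done at that visit and recorded on the Participant Screening Form, and that a positive result is a contraindication under section 3.
3. **Section 9.4, item 7:** describe the pre-randomization test as a repeat for stage II/III women, and keep it.

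When making these edits, it would be sensible to define baseline in exclusion criterion 7 for stage II/III women as before chemoradiotherapy, and to consider a tick in the adjuvant columns for the stage I women described above.

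The three core edits cost one tick, two lines of text and one extra test for a small subgroup at an existing visit where blood is already drawn. Appendix 2 ticks informed consent only before randomization, so the added test would precede trial consent, as the 14 existing pre-radiotherapy rows do. Sample size, randomization and analysis are unchanged.

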### **9.5 Preoperative preparation**

- 1) Anesthesia: general anesthesia with endotracheal intubation.
- 2) Intestinal preparation: An oral laxative is administered 12-24 hours before the operation and finished within 2 to 3 hours.
- 3) Prophylactic use of antibiotics: Antibiotics are intravenously administered 0.5 to 2 hours before surgery or at the beginning of anesthesia, and a second dose can be given more than 3 hours after surgery.

- 4) Other preoperative preparations are performed routinely.

